# PROTOCOL SYNOPSIS

| Acute and long-term effects of intranasal oxytocin in alcohol withdrawal and dependence: A prospective randomized parallel group placebo-controlled trial |
| --- |

| Sponsor | [name], St. Olav’s University Hospital |
| --- | --- |
| Phase and study type | Phase III |
| Investigational Medical Product (IMP) (including active comparator and placebo) : | Syntocinon nasal spray and placebo |
| Center: | Lade Addiction Treatment Center, Central Norway Regional Health Authority |
| Study Period: | Estimated date of first patient enrolled: 01.10.2016  Anticipated recruitment period: 12 months  Estimated date of last patient completed: 01.10.2017 |
| Treatment Duration: | 3 days in-patient treatment, followed by 4 weeks outpatient treatment and phone interview at 8 weeks. |
| Follow-up: | 4 weeks follow-up during outpatient treatment, phone interview at 8 weeks. |
| Objectives | The primary aim of the study is to test whether daily intranasal administration of oxytocin is more effective than placebo in decreasing the oxazepam dosages required to control withdrawal symptoms during a 3-day inpatient program of medical detoxification. The secondary aims are: 1) test whether daily intranasal administration of oxytocin is more effective than placebo in decreasing CIWA-Ar scores during the detoxification period; 2) test the effects on therapist- and self-reported withdrawal symptoms, dysphoria and Actigraph-assessed akathisia and sleep during the detoxification period; and 3) test whether daily intranasal self-administration of oxytocin is more effective than placebo on alcohol use measures (time to ‘relapse’ and amount, cravings), quality of sleep and mood states during a subsequent 4 week out-patient follow-up period. |
| Endpoints: | Primary endpoint: Phase 1: Milligrams of benzodiazepines (oxazepam) used to complete 3 days of detoxification and Actigraph-assessed akathisia and sleep. Phase 2: Time to ‘relapse’ and amount of alcohol intake during 4 weeks of subsequent outpatient treatment.  Secondary endpoint: Phase 1: CIWA-Ar-score, effects on therapist- and self-reported withdrawal symptoms, dysphoria, effects on mood, craving, sleep. |
| Study Design: | Double blind, prospective randomized parallel group placebo-controlled trial. |
| Main Inclusion Criteria: | 1) At least one prior episode 2 days or longer in duration during which the subject experienced withdrawal symptoms that caused significant incapacitation (e.g., inability to work or do normal activities) OR at least one prior inpatient or outpatient medical detoxification during which the subject exhibited withdrawal symptoms of sufficient magnitude that sedative-hypnotic or anticonvulsant medication was required at least once on 2 consecutive days after cessation of or reduction in the use of alcohol following 2 weeks or more of heavy daily consumption; 2) average consumption of 8-30 standard drinks per day for at least 2 weeks prior to enrollment in the study; 3) age 18-65; 4) consenting to participate in the study; 5) have residency in Trøndelag County after discharge |
| Main Exclusion Criteria | 1) chronic treatment with sedative-hypnotic medications such as benzodiazepines or z-hypnotica; 2) dependence on substances other than alcohol, nicotine or caffeine; 3) inadequately treated, unstable and/or compromising medical or psychiatric conditions; 4) low body weight (BMI < 17) or history of anorexia nervosa or bulimia in the past 2 years; 5) pregnancy; parturition or breast-feeding in the past 6 months; 6) inability to read well enough to complete study questionnaires determined by whether the prospective subject can read the consent form without help and correctly answer basic questions about information in the consent form; 7) no alcohol in the blood and > 15 h since last intake of alcohol; 8) prior inclusion and participation in the same study.  Eligible patients will be identified by the intake team and receive information about the trial together with other standard pre-hospitalization information one week before admittance. Patients admitted on short notice will also be eligible for the study. The randomization will be administrated electronically by the Unit of Applied Clinical Research at the Norwegian University of Science and Technology. |
| Sample Size: | 40 patients |
| Efficacy Assessments: | Milligrams of benzodiazepines (oxazepam) needed to complete 3 days of detoxification. |
| Safety Assessments: | Clinical examination, biochemistry/hematology/toxicology and medical history on admittance to decide if patient meet inclution criterias. Negative pregnancytest. CIWA-Ar with vital signs. |

# List of Abbreviations and Definitions of Terms

| **Abbreviation or special term** | **Explanation** |
| --- | --- |
| ACE | Alcohol Craving Experience Questionnaire |
| AE | Adverse Event |
| ACVAS | Alcohol Craving Visual Analog Scale |
| AWS | Alcohol Withdrawal Syndrome |
| AWSC | Alcohol Withdrawal Syndrome Checklist |
| BAI | Beck Anxiety Inventory |
| BDI | Beck Depression Inventori |
| CIWA-Ar | Clinical Institute Withdrawal Assessment-Alcohol revised |
| CNS | Central Nervous System |
| CRF | Case Report Form (electronic/paper) |
| CSA | Clinical Study Agreement |
| CTC | Common Toxicity Criteria |
| CTCAE | Common Terminology Criteria for Adverse Event |
| DAE | Discontinuation due to Adverse Event |
| EC | Ethics Committee, synonymous to Institutional Review Board (IRB) and Independent Ethics Committee (IEC) |
| GABA | gamma-Aminobutyric acid |
| GCP | Good Clinical Practice |
| IB | Investigator’s Brochure |
| ICF | Informed Consent Form |
| ICH | International Conference on Harmonization |
| IMP | Investigational Medicinal Product (includes active comparator and placebo) |
| IND | Investigational New Drug |
| MDMA | 3,4-methylenedioxy-methamphetamine |
| NOMA | Norwegian Medical Agency |
| PAN | Psychotropic Analgesic Nitrous Oxide |
| POMS | Profile of Moods States |
| SAE | Serious Adverse Event |
| SCL-10 | Symptom check list -10 |
| SD | Stable Disease |
| SOP | Standard Operating Procedure |

# introduction

## Background – Alcohol withdrawal syndrome

Alcohol use disorder represents a serious health problem and alcohol dependence is associated with physiological (tolerance and withdrawal) and behavioural (reduced drinking control) symptoms and has interpersonal, social and legal consequences. Alcohol withdrawal syndrome (AWS) is a cluster of symptoms that frequently occur in alcohol-dependent persons and that develops after cessation or reduced intake of alcohol ^1^. Syndromatic symptoms as autonomic and central hyperactivity (sweating, tachycardia, tremor, insomnia, agitation, psychotic symptoms, seizures, anxiety), are mainly due to the GABA-suppressive and glutamate-activating effects of alcohol leading to central nervous system (CNS) hyperactivity in the absence of alcohol. The symptoms may vary from mild to serious and can appear up to 72 hours after last intake (included delirium tremens).Advances in neurobiology and neurochemistry have led to the use of pharmaceuticals in the treatment of alcohol dependence and AWS.

## Background - Therapeutic Information

Common treatments of AWS are benzodiazepines, anticonvulsants, baclofen, gammahydroxy butyrate and psychotropic analgesic nitrous oxide (PAN). Of these only benzodiazepines have shown to perform significantly better than placebo in reducing AWS ^2^. Benzodiazepines have, however, a high potential to be addictive, increase morbidity and mortality, may have depressive respiratory effects when administered in combination with alcohol use, and have limited use in outpatient treatment. At Lade Addiction Treatment Center in Trondheim, oxazepam is the preferred drug to inpatients receiving alcohol detoxification. Doses are given based on withdrawal symptoms measured by Clinical Institute Withdrawal Assessment-Alcohol revised ^3^. Treatment is also supplemented with anticonvulsants and vitamin B following guidelines for dosages.

## Pre-Clinical & Clinical Experience with Oxytocin

Oxytocin is a neuropeptide with synthesis both in the central nervous system and in peripheral tissues such as the uterus, ovaries, testis, vascular endothelium cells and the heart. It is centrally produced by the paraventricular nucleus and the supraoptic nucleus of the hypothalamus, and stored and released from the posterior pituitary into the blood stream (when for example triggered by nipple or vagocervical stimulation). Research suggests that oxytocin has anxiolytic effects and that there is a reciprocal association between positive social stimulation (social bonding) and oxytocin levels^4^. Its anxiety reducing effect has been explored in many studies in the last years as a potential drug to use for patients suffering from psychiatric disorders ^5^. In particular, oxytocin has been suggested to facilitate social reward mechanisms and to support consecutively direct rewarding effects of drugs of abuse ^6^. Brain imaging studies report that MDMA (“ecstasy”) intake, which is associated with central oxytocin release ^7^, alleviates amygdala responses toward unpleasant social stimuli while increasing it toward pleasant stimuli ^8^. Several human studies suggest that intranasal oxytocin increases its concentration in the brain ^9^;^10^;^11^ and enhance social bonding measures^12^, and one study have shown that multiple daily doses reduce psychotic and dissocial schizophrenic symptoms^13^. There are not reported any adverse effects of such oxytocin administration. A review article on intranasal oxytocin in human research showed no detectable subjective changes in recipients, no reliable side effects and was not associated with adverse outcomes in doses of 18-40 IU for short time use^14^. Many animal studies have shown that oxytocin enhance neuroadaptation to alcohol ^15^ and central or peripheral oxytocin reduce alcohol tolerance to the hypothermic, myorelaxant, akinetic and hypnotic effects of alcohol in mice^16^. However, the mechanisms by which oxytocin inhibit tolerance is yet unknown. A small randomized placebo-controlled trial (n=11) of intranasal oxytocin against alcohol withdrawal has recently been conducted ^17^. The authors found that intranasal oxytocin blocked withdrawal symptoms of alcohol in humans as assessed by reduced administration of lorazepam during detoxification, reduced withdrawal symptoms (as measured by the Alcohol Withdrawal Symptom Checklist/AWSC, and the Clinical Institute Withdrawal Assessment for Alcohol score/CIWA) alcohol cravings (as measured by the Alcohol Craving Visual Analog Scale/ACVAS), and tension-anxiety (as measured by the Profile of Mood States/POMS scale). This is the first human indication that alleviated alcohol effects of oxytocin, and the results are consistent with those seen in animal studies.

## Rationale for the Study and Purpose

The study will be conducted at Lade Addiction Treatment Center, Norway. 40 consecutively admitted in-patients undergoing medical detoxification from alcohol at Lade Addiction Treatment Center will be included in the study. In 2014, 150 patients with alcohol dependency as their primary diagnosis were admitted electively to the detoxification unit. If the enrollment of the target number of inclusions exceeds 12 months, the study will seek to include patients from the Clinic of Substance Use and Addiction Medicine at St. Olav’s Hospital.

Oxytocin is neuropeptide hormone which, to our knowledge, is not associated with severe adverse effects. It is a world-wide used, approved, licensed and recommended medicine indicated for the initiation or improvement of uterine contractions in order to achieve vaginal delivery for fetal or maternal reasons. Oxytocin nasal spray is also commonly used by mothers when breastfeeding in the therapy and prophylaxis of mastitis. The potential benefits of the drug as an alternative to benzodiazepine against alcohol withdrawal symptoms, and the benefits of the study are considered greater than the health risks.

In a double blind, prospective randomized parallel group placebo-controlled trial patients will be assigned to receive either oxytocin or placebo which will be administered as a nasal spray twice daily during 3 days of inpatient detoxification, and as a self-administrated spray during a 4-week follow-up period. One arm will receive oxytocin nasal spray, the other arm placebo spray. Patients are randomized in a 1:1 ratio to oxytocin or placebo. The oxytocin will be administered as Syntocinon nasal spray. Syntocinon contains synthetic oxytocin for intranasal use containing 6.7 μg per dose. 1 IU varies between 1.7 μg and 2.2 μg. With 1 IU = 1.7 μg, 1 μg = 0,588 IU, which makes 6.7 μg = 4.34 IU, for practical use 4 IU per dose. We are planning to use 6 insufflations and in total 24 IU given twice daily. This is the same dose of oxytocin as given in a pilot study on human subjects, in which no adverse side effects were reported. The oxytocin dose used by breast-feeding mothers is 6.7 μg.

The placebo spray contains the same ingredients as Syntocinon, except oxytocin.

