# STUDY POPULATION

## Selection of Study Population

The study will be conducted at Lade Addiction Treatment Center, St. Olavs University Hospital, Norway. 40 consecutively admitted in-patients undergoing medical detoxification from alcohol at Lade Addiction Treatment Center will be included in the study.Eligible patients will be identified by the intake team and receive information about the trial together with other standard pre-hospitalization information one week before admittance. Patients admitted on short notice will also be eligible for the study. The randomization will be administrated electronically by the Unit of Applied Clinical Research at the Norwegian University of Science and Technology.

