# Statistical methods and data analysis

## Determination of Sample Size

In a previous study in patients receiving intranasal oxytocin ^17^, the mean dose lorazepam given was 3.4 mg in the oxytocin group and 16.5 mg in the control group. These doses correspond to about 60-70 mg oxazepam and about 320-340 mg oxazepam, respectively. The difference found in that study as well as the does used are, however, rather extreme, and far outside the doses used in both in Norway in general and at Lade Addiction Treatment Center. At Lade Addiction Treatment Center, the oxazepam doses generally range from 0 to 60 mg, with an estimated mean of about 20-30 mg and a SD of about 10 mg. As a difference of 10 mg in oxazepam consumption is of clinical interest to detect between groups, 16 patients in each group are required given an alpha value of 0.05 and a power of 80 %. Therefore, a total of 40 patients will be included in the study.

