## Randomization

Randomization will be performed by Unit of Applied Clinical Research, NTNU.

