## Statistical Analysis

Statistical analysis will be performed by Unit for Applied Research, NTNU.

Descriptive data will be presented as mean ± SD. Dichotomuos outcome variables will be compared using non-parametric test (paired Wilcoxon signed rank test, and McNemar´s test). P-values <0.05 will be considered significant.

0-hypothesis: Oxytocin nasal spray does not differ from placebo in reducing alcohol withdrawal symptoms or decrease craving after detoxification

Primary hypothesis 1: Oxytocin nasal spray can reduce the amount of oxazepam needed to complete 3 days of alcohol detoxification.

Primary hypothesis 2: Oxytocin nasal spray can decrease craving the subsequent 4 weeks after detoxification.

Group comparisons of oxazepam use (measures in mg) at 3 days will be done with student t-test. We will use mixed‐effects regression analyses to examine the change in sleep and actigraph scores from D1 to D3, and changes in anxiety, depression and alcohol use from discharge (D3) to follow-up (D30). Statistics will be performed with per-protocol and intention-to-treat data.Mixed methods take the correlation among repeated measures into account, and they use all available data, thereby lessening concerns about missing data. The basic model will include group (oxytocin, placebo) as the between‐subjects factor and time as the repeated measure. The treatment effect will be evaluated as the group by time interaction, according to the planned comparisons. Both group and time will be fixed‐effects. Covariates can also be added to the models, in order to partial out their effects before evaluating the treatment effects. Follow‐up t‐tests and other post hoc methods will be used to test more time‐ and group‐specific hypotheses. We will test primary hypotheses at the .05 level of significance, but follow‐up and exploratory analyses will be tested at the .01 level of significance.

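### If the contingent second clinic opens, the fixed unadjusted t-test for oxazepam stays valid but loses precision; a clinic term would protect power for one degree of freedom

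*Protocol*

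**What the plan says.** Section 1.4 of the protocol provides for slow recruitment: if enrolment of the target number "exceeds 12 months, the study will seek to include patients from the Clinic of Substance Use and Addiction Medicine" at St. Olav's Hospital. The same section gives the recruitment pool at Lade: "In 2014, 150 patients with alcohol dependency as their primary diagnosis were admitted electively to the detoxification unit".

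Elsewhere the trial is described as a Lade trial. The synopsis names one centre, "Lade Addiction Treatment Center, Central Norway Regional Health Authority", and section 4.1 states that "40 consecutively admitted in-patients undergoing medical detoxification from alcohol at Lade Addiction Treatment Center will be included in the study".

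Section 10.1 plans on Lade's oxazepam use: a mean of about 20-30 mg and an SD of about 10 mg. It sets a 10 mg difference as the target, requires 16 patients per group for 80% power at alpha 0.05, and plans 40 patients in total.

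On allocation, section 1.4 says "Patients are randomized in a 1:1 ratio to oxytocin or placebo" and section 10.2 says "Randomization will be performed by Unit of Applied Clinical Research, NTNU". Section 10.2 mentions neither strata nor blocks and refers to a web page for more on the randomisation service.

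On the analysis, section 10.4 is specific: "Group comparisons of oxazepam use (measures in mg) at 3 days will be done with student t-test". The later sentence that allows covariates is optional, follows the description of the mixed models, and does not name clinic.

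**The concern.** The primary outcome is a quantity of drug given as needed on nurse-rated CIWA-Ar scores. Its mean can differ between clinics through case mix or scoring habit, even under one dosing rule. The protocol foresees a second clinic, yet it names an analysis that cannot use clinic and takes its SD from a single clinic.

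If the two means differ, the t-test counts the between-clinic difference as residual noise. The margin that 40 patients give over the required 32 is then partly or wholly used up. In any one realised trial, an uneven split of the second clinic's patients between arms also shifts the observed difference, and the planned test has no means of correcting this.

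This is more than a detail left to the SAP, because the protocol itself names the test, and the test does not fit a design that the protocol allows.

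**Working it through.** **Inputs from the protocol.** Target difference 10 mg, SD about 10 mg, alpha 0.05, power 80%, 16 per group required, 40 planned (section 10.1); 1:1 allocation (section 1.4); Student t-test (section 10.4).

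**Assumptions not in the protocol.** The second clinic supplies 8 or 12 of the 40 patients (share p = 0.2 or 0.3). Its mean differs from Lade's by D = 5, 10 or 20 mg. The within-clinic SD is 10 mg in both clinics.

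**1. The plan's own figure.** n per group = 2 × (1.960 + 0.842)² × 10² / 10² = 15.7, so 16. This matches section 10.1 with a two-sided alpha (the protocol does not state sidedness). With 20 per arm, the t-test has power 0.87 for 10 mg at SD 10 mg.

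**2. Residual SD without a clinic term.** SD = √(10² + D² × p × (1 − p)). For example, with p = 0.3 and D = 10, SD = √(100 + 100 × 0.21) = 11.0 mg.

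**3. Power at 20 per arm for a true difference of 10 mg.** The t-test column gives the noncentral t result at the SD shown. Simulation with allocation not stratified by clinic agrees within about 0.01. The last column is simulated under the same allocation.

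| From second clinic | Gap D | SD | t-test | Model with clinic term |
|---|---|---|---|---|
| 8 of 40 | 5 mg | 10.2 mg | 0.86 | 0.86 |
| 8 of 40 | 10 mg | 10.8 mg | 0.82 | 0.86 |
| 8 of 40 | 20 mg | 12.8 mg | 0.67 | 0.86 |
| 12 of 40 | 5 mg | 10.3 mg | 0.85 | 0.86 |
| 12 of 40 | 10 mg | 11.0 mg | 0.80 | 0.86 |
| 12 of 40 | 20 mg | 13.6 mg | 0.62 (0.61 simulated) | 0.86 |

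**4. Validity.** In the simulations without clinic strata, the t-test's type I error stayed within 0.047 to 0.053 over these gaps, and the mean arm difference lay within 0.1 mg of the truth.

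**5. Chance imbalance in one trial.** If the second clinic's patients split a:b, the arm contrast shifts by D × (a − b) / 20. With 12 such patients and D = 10, an 8:4 split gives 10 × 4/20 = 2 mg and a 9:3 split gives 10 × 6/20 = 3 mg. When 20 of 40 are allocated to each arm, the hypergeometric probability is 0.30 for 8:4 or worse and 0.08 for 9:3 or worse. At D = 10, the t-test's false-positive rate given the split is 0.031 at 6:6, 0.066 at 8:4 and 0.113 at 9:3. Averaged over all splits it is 0.05.

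**6. What strata alone would do.** With allocation stratified by clinic and the unadjusted t-test kept, power is 0.81 to 0.83 at 10 mg and 0.60 to 0.70 at 20 mg (8 to 20 patients from the second clinic). The test also becomes conservative, with type I error 0.029 to 0.036 at 10 mg. Nearly all the gain therefore comes from the clinic term.

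**The case against.** The case for leaving the plan alone has several good parts.

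- **The risk is conditional.** The clinic is sought only if enrolment runs past 12 months, and 40 patients are needed against 150 elective admissions in 2014. Opening it would be a natural moment for an amendment under section 11.3. This stands, and it lowers the priority. The sponsor nevertheless planned for the event, and stating the analysis now avoids choosing it later.
- **Nothing points to a large gap.** Section 10.1 calls the earlier trial's doses "far outside the doses used in both in Norway in general and at Lade Addiction Treatment Center", which groups Lade with Norwegian practice. The second clinic is also Norwegian and at St. Olav's, and section 7.2 applies one symptom-triggered order set to every included patient. This stands too: the contrast with the earlier trial is no evidence of a 20 mg gap between these two clinics.
- **The planned power largely survives.** Even at a 10 mg gap, as large as the target effect, power is 0.80 to 0.82. This is correct.

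Three stronger readings are tempting, and the documents do not support them. A reader might infer that the type I error is inflated, but it stays at about 5%. A reader might infer that the treatment estimate is biased, but the shift is chance imbalance in a single realisation, which the t-test's standard error covers on average. A reader might also infer that allocation will ignore clinic, but section 10.2 is simply silent on strata, and such details are commonly held elsewhere.

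What the objection does not remove is that section 10.4 names a test without clinic for a design that may have two clinics.

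**Conclusion.** The point holds as a matter of precision. The protocol allows a second clinic, describes and plans for Lade alone, and fixes a primary test that cannot take clinic into account. The loss against a model with a clinic term is negligible at a 5 mg gap, about 4 to 6 percentage points at 10 mg, and about 19 to 25 points at 20 mg. It would be wrong to say that the stated 80% power is lost in general: that requires a gap clearly above 10 mg, which the protocol neither gives nor suggests.

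These figures rest on the assumed share of 8 to 12 patients, the assumed gaps and a common within-clinic SD of 10 mg. This is a cheap improvement with a benefit only if the second clinic opens. Priority: consider.

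**What to change.** In section 10.4, state that if a second clinic contributes patients, oxazepam mg will be compared by a linear model with arm and clinic. If only Lade recruits, the model contains arm alone and is the planned Student t-test.

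Mention the contingent clinic in the synopsis and in section 4.1, so that they agree with section 1.4.

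Stratifying the WebCRF allocation by clinic is an optional supplement. It prevents uneven splits but recovers little power without the clinic term.

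The cost is one sentence of analysis text, two wording changes and one degree of freedom (37 instead of 38 with 40 patients). If the two clinics turn out not to differ, power falls by about 0.01, from 0.87 to 0.86. If the clinic never opens, the analysis is unchanged.

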## Exclusion Criteria

Patients will be excluded from the study if they meet any of the following criteria:

- No alcohol in the blood and more than 15 h since last intake of alcohol at admission
- Adverse reactions to some of the ingredients of Syntoinon nasal spray, e.g. allergic reactions to methyl- and propylparahydroksybenzoat (E 216, E 218) or hereditary fructose intolerance
- Chronic treatment with sedative-hypnotic medications such as benzodiazepines or z-hypnotica
- Dependence on substances other than alcohol, nicotine or caffeine
- Inadequately treated, unstable and/or compromising medical or psychiatric conditions
- Low body weight (BMI < 17) or history of anorexia nervosa or bulimia in the past 2 years
- Pregnancy (females at fertile age will undergo pregnancy testing upon admission); parturition or breast-feeding in the past 6 months; females at fertile age not using oral contraceptives or other hormonal conctaceptive products (patch, i.m. depot injections, ring, implant, IUD).
- Inability to read well enough or understand to complete study questionnaires determined by whether the prospective subject can read the consent form without help and correctly answer basic questions about information in the consent form
- Concomitant participation in another medical clinical trial
- Prior inclusion and participation in the same study.
- Any reason why, in the opinion of the investigator, the patient should not participate.

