**IMP and placebo**

The company Sanivo Pharma AS, previously known as Farmaholding (www.farmaholding.no) will decanter Syntocinon into 10 ml amber glass bottles. The company will also manufacture placebo in identical bottles. The study drug will be decanted to new nasal spray containers, following a Class D regimen. Since the production of placebo and the production of Syntocinon take place in two different locations, testing of absence of oxytocin is considered to be unnecessary.

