### Allocation- procedure to randomize a patient

Preparation of active drug or placebo will produce identical nasal sprays. Who to receive the active drug will be determined by electronic randomization executed with WebCRF, provided by the Unit of Applied Clinical Research at the Norwegian University of Science and Technology (NTNU). More information on the randomization services from the Unit of Applied Clinical Research can be found at <http://www.ntnu.edu/dmf/akf/randomisering>.

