# Appendix C – Placebo decleration list

| **Syntocinon/Placebo Nasal Spray #2** | |  |
| --- | --- | --- |
| **5ml** |  |  |
|  |  |  |
| Chlorobutanol, NF (Anhydrous) | 0,013 | gm |
| Methylparaben, NF | 0,002 | gm |
| Propylparaben, NF | 0,001 | gm |
| Citric Acid, USP (Anhydrous) | 0,014 | gm |
| Sodium Chloride, USP (Granular) | 0,025 | gm |
| Sodium Phosphate Dibasic, USP | 0,01 | gm |
| Glycerin, USP | 0,25 | ml |
| QS |  |  |
| Purified Water, USP | 5 | ml |

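### The protocol contradicts itself on excipients: the exclusion criteria imply a fructose source in Syntocinon, the Appendix C placebo formula contains none, and the matched-placebo claim is therefore unverified

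*Protocol*

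**What the plan says.** Section 1.4 of the protocol (Rationale for the Study and Purpose) defines the comparator: "The placebo spray contains the same ingredients as Syntocinon, except oxytocin". Section 10.2.1 (Allocation) relies on this: "Preparation of active drug or placebo will produce identical nasal sprays".

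Section 4.4 (Exclusion Criteria) bars patients who react badly to components of the product; its wording refers to "ingredients of Syntoinon nasal spray, e.g. allergic reactions to methyl- and propylparahydroksybenzoat (E 216, E 218) or hereditary fructose intolerance".

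Appendix C, the placebo declaration list, carries the table heading "Syntocinon/Placebo Nasal Spray #2". It lists chlorobutanol, methylparaben, propylparaben, anhydrous citric acid, sodium chloride, dibasic sodium phosphate, glycerin and purified water, made up to 5 ml.

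Under section 5.1, one company decants marketed Syntocinon into amber glass bottles and also manufactures the placebo in identical bottles. The tests specified for both products are pH and microbiological quality.

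**The concern.** The active spray is a marketed product moved into new bottles, while the placebo is made separately to its own formula. The two match only if the Appendix C formula reproduces the excipients of the marketed product. The one place where the protocol lets a reader check this from the inside is the exclusion criterion that names Syntocinon ingredients, and on fructose that check fails.

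The stake is the comparator. Any excipient difference would coincide exactly with treatment arm, so the trial would no longer compare oxytocin with the same vehicle without oxytocin. Matching also supports the blind, and the primary endpoint depends on the blind. Oxazepam is given according to CIWA-Ar scores (sections 7.1 and 7.2), and several items in Appendix B, such as headache, nausea, anxiety and the sensory items, start from a question to the patient. A single triggered dose is 10 or 15 mg, against a between-group difference of 10 mg for which the trial is sized (section 10.1). If the mistake lies in section 4.4 instead, the placebo may be sound, but an eligibility criterion misdescribes the product.

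**Working it through.** The protocol gives no figure on this point, so the check is a comparison of passages.

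**1. Ingredients implied by section 4.4, looked up in Appendix C**

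| Implied by section 4.4 | In Appendix C? |
| --- | --- |
| Methyl parahydroxybenzoate | Yes: "Methylparaben, NF", 0.002 g per 5 ml |
| Propyl parahydroxybenzoate | Yes: "Propylparaben, NF", 0.001 g per 5 ml |
| A fructose source (hereditary fructose intolerance) | No: 0 of 8 components |

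The eight components include no fructose, sucrose or sorbitol. Glycerin is the only polyol listed, and it is not a fructose source.

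**2. Is the list complete?** It ends with purified water to a final volume of 5 ml, as a closed formula does, and shows no sign of removed text. The absence of a fructose source can be taken as stated.

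**3. Can the three statements hold together?**
- If section 4.4 is right that Syntocinon contains something relevant to fructose intolerance, and Appendix C is the placebo as made, then the statement in section 1.4 is false.
- If sections 1.4 and Appendix C are right, then Syntocinon contains no fructose source and the ingredient reference in section 4.4 is wrong.
- If sections 1.4 and 4.4 are right, then Appendix C is incomplete or the wrong version.

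At least one of the three needs correction. The protocol contains no separate excipient list for the marketed spray, so it cannot show which.

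**4. Would a planned test expose a mismatch?** The microbiological tests look for contamination. A sugar or sugar alcohol need not alter pH, and section 5.1 states no criterion for agreement in pH between the two products. The oxytocin measurements in section 5.1 are made on decanted Syntocinon only and concern the active ingredient. None of these tests is designed to detect a missing excipient.

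**The case against.** The best defence is that most of the protocol points one way. Sections 1.4 and 10.2.1 and Appendix C agree with each other, the Appendix C heading names Syntocinon and placebo together as if one formula served both, and both named parabens are present. The outlier is an example in one exclusion criterion, which might be read as naming a separate condition and not a reaction to an ingredient. On that view one phrase needs editing and the placebo is sound.

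This may turn out to be correct, but the protocol does not establish it. The list contains no oxytocin, so it can only be the placebo formula, whatever its heading; it is not an independent declaration of what marketed Syntocinon contains. The fructose example stands inside a criterion about ingredients of the spray, and fructose has no other role in the protocol.

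A reader might infer more: that the placebo is known to be mismatched, or that the blind has failed. Neither is supported. No passage says the sprays differ in taste, smell or feel. Each patient receives one product and so has no second spray to compare. Bottles are identical, and section 10.2.2 blinds patients, investigator, outcome assessors and analyst. Tremor, sweating and agitation are scored by observation alone. Any inflated false-positive rate would have to start from an assumed shift in oxazepam use, which the protocol does not give, and would only restate that assumption.

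A reader might also link this to section 5.1, where "testing of absence of oxytocin is considered to be unnecessary". That waiver concerns mix-up of active and placebo, which is a different question. The protocol gives no basis for a swap rate, and the excipient contradiction neither supports nor needs that argument.

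**Conclusion.** The contradiction between section 1.4, section 4.4 and Appendix C is real and stands on the page. Its consequence is limited: the matched-placebo claim in sections 1.4 and 10.2.1 is unverified, not shown to be false. The conclusion rests on two readings: that Appendix C is the complete placebo formula, and that section 4.4 means what its wording says, namely that fructose intolerance matters because of an ingredient of the spray.

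No bias can be quantified from the document, and no sample-size, power or error-rate figure in section 10 changes. Unblinding remains a possible consequence, worth excluding because oxazepam dosing follows CIWA-Ar scores that are partly patient-reported. The point merits action before placebo release because the check is small, and a mismatch found after the trial could not be repaired.

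**What to change.** Before any placebo is released, compare Appendix C line by line with the declared excipients of the Syntocinon being decanted, and file the comparison.

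- If an excipient is missing from the placebo, add it at the same concentration as in the active spray and reissue Appendix C.
- If none is missing, leave the formula alone and reconcile the ingredient reference in section 4.4 with the product's actual ingredients.

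In either case sections 1.4, 4.4 and 10.2.1 and Appendix C should agree afterwards.

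The cost is one document check and a correction to the protocol, with no added patients, visits or assays. The main downside is that a placebo batch already filled to an incomplete formula may have to be remade.
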